## Abstract

**Background:**

Prolonged disorders of consciousness (pDoC), encompassing vegetative state (VS) and minimally conscious state (MCS), represent a formidable clinical challenge characterized by substantial uncertainty in prognostic assessment. Although prior studies have yielded several short-term observational findings, large-scale, long-term longitudinal data delineating the 5-year natural history of pDoC remain scarce—particularly within the Chinese healthcare context. Moreover, existing studies have frequently lacked standardized multimodal assessment protocols and have failed to account for competing risks (e.g., mortality) in statistical models, thereby limiting the accuracy of currently available prognostic tools. The present study aims to address this critical evidence gap through the establishment of a high-quality prospective cohort.

**Methods:**

The PDOCC study is a single-center, prospective cohort investigating 5-year disease trajectories in 1,000 patients (aged 18–80) with prolonged disorders of consciousness (VS or MCS ≥ 28 days post-brain injury) (traumatic and non-traumatic etiologies) enrolled at Guangdong Sanjiu Brain Hospital. Data collection includes standardized clinical assessments (CRS-R, GOS-E, DRS, EQ-5D, SF-36), neuroimaging (MRI/DTI/fMRI), and biomarkers (NfL, GFAP, S100B). Follow-up assessments at 3, 6, 12, 24, 36, 48, and 60 months combine in-person evaluations (all timepoints) with remote telephone interviews (3-month intervals after the 6-month visit). Neuroimaging and biomarkers are assessed at baseline and at 6, 12, 24, 36, 48 and 60 months. Primary outcomes are: (1) consciousness recovery, defined as emergence from MCS (eMCS) according to the CRS-R criteria (i.e., consistent functional communication and/or functional object use) sustained for ≥4 consecutive weeks; (2) all-cause mortality; and (3) major cardiovascular events (myocardial infarction, heart failure hospitalization, stroke). Secondary outcomes include: (1) functional status changes (GOS-E, DRS); (2) dynamic biomarker changes (NfL, S100B, GFAP); (3) health-related quality of life (EQ-5D); and (4) rehospitalization rate. Time-to-event analyses will use Fine-Gray competing-risk models to account for mortality as a competing event. Prognostic prediction modeling will be conducted in three sequential stages: a clinical model, a neuroimaging-augmented model (DTI/fMRI), and a fully integrated multimodal model additionally incorporating serum biomarkers (NfL, GFAP, S100B).

**Discussion:**

The PDOCC study will generate the first comprehensive longitudinal dataset characterizing long-term (5-year) outcomes of pDoC in a southern Chinese population. Through the incorporation of competing-risk analysis and a hybrid follow-up strategy, this protocol mitigates methodological biases that are prevalent in disorders of consciousness (DoC) research. The prognostic prediction models developed are anticipated to inform individualized rehabilitation decision-making, optimize the allocation of healthcare resources, and provide a methodological framework for future multicenter collaborative investigations.

**Clinical trial registration:**

https://www.chictr.org.cn/bin/project/edit?pid=246240, Identifier ChiCTR2400091315.

## Introduction

### Background and rationale

Prolonged disorders of consciousness (pDoC) constitute a clinical syndrome resulting from severe acquired brain injury, encompassing a diagnostic spectrum from vegetative state (VS) and minimally conscious state (MCS; further divided into MCS − and MCS+) through to emergence from MCS (eMCS) and, in the context of traumatic brain injury, post-traumatic confusional state (PTCS) as upper-boundary transitional states (1). Traumatic brain injury (TBI) represents one of the most prevalent etiologies of DoC, inducing diffuse axonal injury and multifocal cortico-subcortical network dysfunction that culminate in sustained impairment of conscious awareness (2). Although a subset of patients achieves meaningful functional recovery within the first year following injury, prolonged disorders of consciousness continue to pose a formidable clinical challenge. Notably, early functional deficits in the acute aftermath of severe brain injury do not necessarily portend an unfavorable long-term prognosis; for instance, among patients with moderate-to-severe TBI, the majority recover consciousness within 12 months even when an initial vegetative state is observed (3).

Multiple critical knowledge gaps persist in the current management of DoC. Neuroimaging and neurophysiological techniques have demonstrated capacity to detect “covert consciousness” in up to 15–20% of behaviorally unresponsive patients; however, routine clinical deployment of these modalities remains constrained by technical complexity, cost, and the requisite expertise for interpretation (1). Although functional neuroimaging modalities—including functional MRI (fMRI), electroencephalography (EEG), and positron emission tomography (PET)—have been shown to facilitate diagnosis and prognostication, and to predict recovery potential under specific circumstances, substantial practical barriers impede their widespread implementation (4). Furthermore, while multimodal assessment has been validated as a reliable predictor of unfavorable neurological outcomes in comatose survivors of cardiac arrest, the applicability of such strategies to DoC arising from alternative etiologies—such as stroke or hypoxic–ischemic encephalopathy—remains uncertain (5). Collectively, these limitations underscore the urgent need for high-quality prospective investigations that integrate standardized clinical assessment, advanced neurological monitoring, and longitudinal follow-up data.

### Study objectives

This study aims to systematically characterize the 5-year natural history of pDoC through a prospective cohort design, thereby bridging the critical evidence gap stemming from the absence of large-scale, long-term follow-up investigations. The specific objectives are as follows:To determine the rates of consciousness recovery, all-cause mortality, and major cardiovascular events over a 5-year follow-up period in patients stratified by initial level of consciousness (VS, MCS−, and MCS+); primary comparisons will be conducted at the VS vs. MCS level, with MCS − vs. MCS + differentiation examined in prespecified subgroup analyses.To identify etiology, injury severity (GCS at admission), time from injury to enrollment, Coma Recovery Scale–Revised (CRS-R) subscale profiles, and neuroimaging indices as independent predictors of consciousness recovery and unfavorable outcomes.To develop and validate a multimodal prognostic prediction model integrating clinical, neuroimaging, and biomarker data.

The primary research question of this study is: among patients with prolonged disorders of consciousness (VS or MCS ≥ 28 days post-acute brain injury), does baseline consciousness level (VS vs. MCS) independently predict 5-year consciousness recovery trajectory, after adjustment for etiology, injury severity, and neuroimaging characteristics?

## Methods

### Study design and setting

The Prolonged Disorders of Consciousness Cohort (PDOCC) study is a single-center, prospective cohort study designed to systematically characterize the 5-year natural history and prognostic determinants of VS and MCS. A total of 1,000 eligible participants are planned for enrollment between June 2026 and May 2029, with longitudinal follow-up conducted over 5 years via structured telephone interviews at 3-month intervals. The study will be conducted at the Department of Rehabilitation Medicine, Guangdong Sanjiu Brain Hospital. The enrollment period spans from June 1, 2026 to May 31, 2029 (36 months). The follow-up period is calculated from each participant’s date of enrollment and extends for 60 months, with full cohort follow-up to be completed by May 31, 2034. Data collection encompasses a baseline assessment at enrollment and scheduled follow-up visits at 3, 6, 12, 24, 36, 48, and 60 months. The study protocol has been approved by the Institutional Review Board of Guangdong Sanjiu Brain Hospital (Ethics Approval No. 2026-01-073). Written informed consent will be obtained from all participants or their legally authorized representatives (LARs) prior to enrollment.

### Study population

The target population comprises individuals currently diagnosed with pDoC—specifically VS or MCS (encompassing both MCS − and MCS+)—at the time of enrollment. Patients who have already achieved eMCS prior to enrollment are not eligible, as eMCS constitutes the primary consciousness recovery endpoint of this study. Patients with post-traumatic confusional state (PTCS), which represents a transitional state beyond eMCS in the TBI recovery trajectory, are likewise not eligible for enrollment. Both conditions are characterized by persistent alterations in consciousness following severe acquired brain injury: VS is defined by wakefulness without awareness, whereas MCS indicates the preservation of partial conscious awareness.

Inclusion criteria are as follows: (1) a confirmed diagnosis of DoC with a duration of at least 28 days, established according to the 2020 European Academy of Neurology (EAN) guidelines (6) and assessed using the validated Chinese version of the CRS-R (7), including vegetative state (VS) and minimally conscious state (MCS; encompassing both MCS − and MCS+); (2) age between 18 and 80 years; (3) provision of written informed consent by the participant (if possessing decision-making capacity) or by a legally authorized representative (LAR); and (4) availability of complete medical records documenting the etiology of the initial brain injury, injury severity, and relevant diagnostic investigations. Eligible etiologies include all forms of acquired brain injury that can lead to prolonged disorders of consciousness (pDoC), such as traumatic brain injury (including both closed and penetrating head injuries) and non-traumatic brain injury—including hypoxic-anoxic injury (e.g., due to cardiac arrest, respiratory failure, or near-drowning), cerebrovascular events (such as ischemic stroke, hemorrhagic stroke, and subarachnoid hemorrhage), and metabolic or toxic encephalopathies.

Exclusion criteria include: (1) transient disorders of consciousness resulting from acute brain injury with a duration of fewer than 28 days; (2) severe organ dysfunction, defined as New York Heart Association (NYHA) Class III–IV heart failure, Child-Pugh Class C cirrhosis, or end-stage renal disease with an estimated glomerular filtration rate (eGFR) < 15 mL/min/1.73 m^2^; (3) irreversible end-stage disease, including TNM Stage IV metastatic malignancy or progressive neurodegenerative disease (e.g., Alzheimer’s disease, Parkinson’s disease, amyotrophic lateral sclerosis), given that consciousness impairment in these conditions may reflect primary disease progression rather than post-injury pDoC; (4) inability to comply with the study protocol, such as residing more than 200 km from the study site, presence of severe communication barriers, or explicit refusal of follow-up; and (5) severe comorbid orthopedic or internal injuries (e.g., unstable spinal fracture, severe polytrauma with active hemorrhagic shock) that preclude safe administration of CRS-R or neuroimaging protocols, or that are judged by the attending neurologist to render behavioral consciousness assessment invalid. Patients with non-confounding orthopedic injuries (e.g., healed limb fractures not affecting motor command assessment) are not excluded; all such comorbidities will be documented and incorporated as covariates. Pre-existing stable neurological diagnoses (e.g., prior cerebrovascular events, epilepsy) will be recorded as comorbidities and adjusted for in all multivariable models rather than treated as grounds for exclusion.

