### Subgroup and interaction analyses

Prespecified subgroup analyses will be conducted based on clinical relevance and potential effect modification, including: age (< 50 years vs. ≥ 50 years), sex (male vs. female), injury type (traumatic vs. non-traumatic), and baseline level of consciousness (VS vs. MCS). Interaction terms (product terms between the exposure variable and subgroup variables) will be introduced into multivariable regression models to formally test the statistical significance of interactions, with a significance threshold of *p* < 0.10. Statistically significant interactions will be further examined through stratified subgroup analyses, with results displayed as forest plots showing HRs and 95% CIs for each subgroup. All subgroup analyses will be characterized as exploratory findings to prevent overinterpretation.

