This study achieves several important methodological advances. The rigorous prospective longitudinal design, with a 5-year follow-up period substantially exceeding that of most published studies (typically 1–2 years), enables comprehensive characterization of both the critical time windows for consciousness recovery and the features of long-term stable plateaus—directly addressing the predominant reliance on cross-sectional observations in the field and providing unprecedented longitudinal data to elucidate the time-dependent nature of recovery. In terms of data integration, this protocol transcends the limitations of traditional single-source clinical data by harmonizing structured electronic medical records, standardized neuropsychological assessments (CRS-R), objective neuroimaging (structural and functional MRI), serum biomarkers of neural injury, and patient-reported outcomes (health-related quality of life instruments). Notably, the application of internationally standardized instruments with blinded assessment for the definition of core outcome variables substantially reduces misclassification and information bias. This multisource data integration is anticipated to reveal deep associations between clinical phenotypes and biological mechanisms, uncovering interaction patterns that conventional single-modality research cannot identify. To mitigate the most critical methodological threats in DoC research—attrition bias and measurement bias—we have implemented distinctive safeguards: a hybrid follow-up strategy combining telephone interviews and outpatient visits, with a quality target of ≥ 85% follow-up completion rate; uniform training and certification of all assessors; blinded adjudication of all primary outcome events by an independent Endpoint Adjudication Committee; and independent dual-reader review of all neuroimaging data. As a single-center study, we are able to achieve a highly standardized operational workflow and quality control system, with all data collection adhering to unified standard operating procedures (SOPs). The study has been prospectively registered on an international clinical trial registry and will be reported in compliance with the STROBE statement; the level of quality control substantially exceeds the average for comparable observational studies.

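### With no upper limit on time since injury and a clock that starts at enrolment, the pooled 5-year recovery curves depend on referral timing if the recovery hazard falls over time, and cannot by themselves show natural history or recovery windows

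*Protocol article*

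**What the plan says.** All references are to the protocol article.

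- **Entry (Study population).** The inclusion criterion is "a confirmed diagnosis of DoC with a duration of at least 28 days". The only exclusion on duration repeats that floor: "transient disorders of consciousness resulting from acute brain injury with a duration of fewer than 28 days". No criterion sets an upper limit on time since injury.
- **Selection at entry (Study population).** "Patients who have already achieved eMCS prior to enrollment are not eligible". Patients who died before referral cannot enter either. Recruitment procedures describe entry by referral to one rehabilitation department.
- **Clock (Study design and setting).** Follow-up counts from each participant's "date of enrollment and extends for 60 months".
- **Descriptive target (Study objectives).** Objective 1 is the 5-year rates of recovery, death and cardiovascular events by VS, MCS− and MCS+. The stated aim is the 5-year natural history. The Discussion adds that the design "enables comprehensive characterization of both the critical time windows for consciousness recovery and the features of long-term stable plateaus".
- **Time from injury in the analysis.** It is recorded and named a primary predictor (Predictor variables and covariates). It enters Models 3 to 5 (Primary analysis), the nested comparison and the clinical prediction model. It is not mentioned where the cumulative incidence functions are described. It is also absent from the effect modifiers and from the subgroup list, which is age, sex, "injury type (traumatic vs. non-traumatic), and baseline level of consciousness (VS vs. MCS").

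**The concern.** A patient 29 days after injury and a patient several years after injury can both enter at time zero. Month 12 of the study is then about 13 months after injury for the first and years after injury for the second. The later entrant has also been selected for having neither died nor recovered in the meantime.

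The section on predictors says that the interval from injury to enrolment has an established direct effect on recovery. If so, the pooled curve reflects the referral pattern of one department as well as the disease. Another centre with the same patients but earlier or later referral would report a different 5-year recovery rate. A steep or flat part of a curve drawn on the enrolment clock has no fixed meaning in disease time, so a recovery window or plateau cannot be read from it.

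What is at stake is the descriptive output: Objective 1's recovery rates, the cumulative incidence curves and the unadjusted group curves. Families and clinicians would read these as time after injury.

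**Working it through.** **1. The article's own figure.** Sample size calculation gives an annual event rate of 8% and a 5-year recovery incidence of 34%. The check is 1 − (1 − 0.08)^5 = 1 − 0.92^5 = 34.1%, so the figure reproduces. The conversion applies the same annual rate in every year after enrolment, whatever the time since injury.

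**2. Illustration of dependence on entry time.** The documents give no distribution of entry times and no hazard shape, so the following are assumptions:

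- recovery hazard at s months since injury: λ·k·s^(k−1). It is constant for k = 1 and declines for k < 1;
- death: 10% per year, constant, so μ = −ln(0.9)/12 = 0.00878 per month;
- λ set so that entry at day 28 (28/30.4 = 0.92 months) gives the article's 34%. This yields λ = 0.0093, 0.0315, 0.0746 and 0.2004 for k = 1, 0.7, 0.5 and 0.3.

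For entry at e months, the 5-year recovery incidence from enrolment is the integral over t from 0 to 60 of λ·k·(e+t)^(k−1) · exp{−λ[(e+t)^k − e^k] − μt}.

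| Hazard shape k | Day 28 | 3 months | 6 months | 12 months | 24 months |
|---|---|---|---|---|---|
| 1 (constant) | 34.0% | 34.0% | 34.0% | 34.0% | 34.0% |
| 0.7 | 34.0% | 32.5% | 31.2% | 29.3% | 27.0% |
| 0.5 | 34.0% | 31.1% | 28.6% | 25.6% | 22.1% |
| 0.3 | 34.0% | 29.1% | 25.6% | 21.5% | 17.2% |

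Annual death of 5% or 15% instead of 10% moves these figures by about one point or less.

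**3. Effect on the pooled rate.** With half the cohort entering at day 28 and half at 24 months, the pooled figure is (34.0 + 27.0)/2 = 30.5% for k = 0.7 and (34.0 + 17.2)/2 = 25.6% for k = 0.3. Only referral timing has changed.

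**4. A harsher shape.** Take recovery at 0.6 per year until 12 months after injury and 0.03 or 0.06 per year afterwards, with death at 0.10 per year. Entry at 1 month gives 45.6% or 50.1%, and entry after 12 months gives 11.0% or 20.7%. With 60% late entrants the pooled figure is about 25% or 32%. This assumes a 10- to 20-fold fall in hazard at one point in time, so it shows how far the effect could go and is not an expected size.

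**5. All-cause mortality.** The outcome section defines this as death at any point in 60 months, and recovery does not end follow-up for it. With 10% per year throughout, it is 1 − 0.9^5 = 41.0% at every entry time. Death before recovery does move, from 29.9% (day 28) to 36.2% (24 months) at k = 0.3, but only because fewer patients recover first. That is not the mortality outcome as defined.

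**The case against.** The strongest defence is that prognosis from enrolment is a legitimate quantity. The target population is patients with a current diagnosis at enrolment, and a clinician meeting such a patient needs exactly that figure. This stands, provided the rate is labelled that way; the article labels it natural history.

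The primary question is also largely protected. It concerns VS versus MCS after adjustment, and time from injury is in Models 3 to 5. The Primary analysis section also tests proportional hazards and lists time-varying covariates, stratification and splines as remedies. This too stands, and it limits the point to absolute recovery rates, time windows and unadjusted curves, which none of those measures alters.

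Banding and the choice of time scale could be seen as details for an analysis plan. That stands only in part: the article itself fixes the eligibility, the clock, the strata and the subgroup list, and then draws claims from them.

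A reader might infer more than the documents support:

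- **That all-cause mortality also shifts with entry time.** Step 5 of the working shows no shift under a constant death hazard, and the documents give no other death hazard.
- **That the rates cannot be compared with the cited 42.3% to 48.7%.** The time origin and entry window of those cohorts are not shown.
- **That recovery in all pDoC is confined to the first year.** The Background statement that "the majority recover consciousness within 12 months even when an initial vegetative state is observed" concerns moderate-to-severe TBI only, and the Discussion expects recoveries beyond 12 months.
- **That VS and MCS curves will differ spuriously.** This needs different referral timing in the two groups, for which there is no evidence in the article.

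**Conclusion.** The point holds for the descriptive recovery results. A 28-day floor without a ceiling, combined with an enrolment clock, gives pooled recovery curves that average over uncontrolled disease times in patients selected as alive and unrecovered. Those curves cannot by themselves show the natural history, recovery windows or plateaus that the article claims.

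The size cannot be determined from the documents. Under a declining hazard anchored at 34% for day-28 entry, entry at 24 months gives about 17% to 27%; under a constant hazard nothing changes. That the hazard declines is an assumption: the article states a direct effect of the interval on recovery but gives no shape. The adjusted VS versus MCS comparison is not seriously threatened. The change should be made, and before enrolment begins, so that the bands are not chosen after seeing outcomes.

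**What to change.** Leave eligibility unchanged and amend the analysis and wording:

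1. Report the recovery cumulative incidence by prespecified bands of time from injury to enrolment (for example 28–90 days, 91–365 days and over 365 days), overall and by VS/MCS, alongside the pooled figure. Show mortality by the same bands descriptively.
2. Base any statement about recovery windows or plateaus on the cause-specific model already planned under Sensitivity analyses, fitted on time since injury with delayed entry at enrolment.
3. Add time from injury to the list under Subgroup and interaction analyses.
4. Describe pooled rates as counted from enrolment in a cohort of mixed time since injury, and remove the natural-history label from them.

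The interval is already collected, so the cost is protocol or analysis-plan wording, a few more tables, and wider confidence intervals in the smaller bands.
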